## Abstract

**Background:**

Digitalization and information and communication technology (ICT) promote effective, efficient individual and community care. Clinical terminology or taxonomy and its framework visualize individual patients’ and nursing interventions’ classifications to improve their outcomes and care quality. Public health nurses (PHNs) provide lifelong individual care and community-based activities while developing projects to promote community health. The linkage between these practices and clinical assessment remains tacit. Owing to Japan’s lagging digitalization, supervisory PHNs face difficulties in monitoring each department’s activities and staff members’ performances and competencies. Randomly selected prefectural or municipal PHNs collect data on daily activities and required hours every 3 years. No study has adopted these data for public health nursing care management. PHNs need ICTs to manage their work and improve care quality; it may help identify health needs and suggest best public health nursing practices.

**Objective:**

We aim to develop and validate an electronic recording and management system for evaluating different public health nursing practice needs, including individual care, community-based activities, and project development, and for determining their best practices.

**Methods:**

We used a 2-phase exploratory sequential design (in Japan) comprising 2 phases. In phase 1, we developed the system’s architectural framework and a hypothetical algorithm to determine the need for practice review through a literature review and a panel discussion. We designed a cloud-based practice recording system, including a daily record system and a termly review system. The panels included 3 supervisors who were prior PHNs at the prefectural or municipal government, and 1 was the executive director of the Japanese Nursing Association. The panels agreed that the draft architectural framework and hypothetical algorithm were reasonable. The system was not linked to electronic nursing records to protect patient privacy. Phase 2 validated each item through interviews with supervisory PHNs using a web-based meeting system. A nationwide survey was distributed to supervisory and midcareer PHNs across local governments.

**Results:**

This study was funded in March 2022 and approved by all ethics review boards from July to September and November 2022. Data collection was completed in January 2023. Five PHNs participated in the interviews. In the nationwide survey, responses were obtained from 177 local governments of supervisory PHNs and 196 midcareer ones.

**Conclusions:**

This study will reveal PHNs’ tacit knowledge about their practices, assess needs for different approaches, and determine best practices. Additionally, this study will promote ICT-based practices in public health nursing. The system will enable PHNs to record their daily activities and share them with their supervisors to reflect on and improve their performance, and the quality of care to promote health equity in community settings. The system will support supervisory PHNs in creating performance benchmarks for their staff and departments to promote evidence-based human resource development and management.

**Trial Registration:**

UMIN-ICDR UMIN000049411; https://tinyurl.com/yfvxscfm

**International Registered Report Identifier (IRRID):**

DERR1-10.2196/45342

## Introduction

### Background

Digital technologies promote innovation in health care and nursing [1]. Notably, a previous study categorized different applications of information and communication technology (ICT) in nursing practice into assessment, clinical intervention, health promotion, and service organization [2]. Regarding assessment, nurses have used electronic clinical recording systems [3] to assist in clinical decision-making for individual care [4], meet patients’ health needs [5], and reduce overwork time and medical care expenditure [6]. Meanwhile, ICT-based health promotion programs can improve community health [7]. ICT also ensures efficient staffing and supports health workers’ decision-making, communication, training, and health system management [1]. Therefore, digitalization and ICT promote effective and efficient care for individuals and communities. However, previous research has primarily focused on hospital- or clinic-based individual care [8]; little work has been done on the function of ICT in public health nursing [2].

Clinical terminology or taxonomy and its framework help visualize the classification of patients and nursing practice and improve health equity in multidisciplinary settings [9-14]. Nursing practices are based on nursing diagnosis systems [11] and interventions [12]. Focusing on patient outcomes is essential to improve nursing care and management quality [13,14]. However, while prior studies examine individual patients, knowledge about public health nursing is scarce. Under each country's different cultures, policies, and health care systems, public health nurses (PHNs) provide a wide range of lifelong care, support at the group level, and community-based activities. They also create policies, programs, projects, and health care systems that meet the needs of each community [15]. Individual care takes up most of a PHN’s time [16], making it difficult to perform community-based activities and assessments [17], which are the basis of developing needs-oriented projects. Although these projects are vital for improving health equity in the community [18], evaluating the necessity of these practices and their linkage depends on the PHN’s tacit knowledge. Therefore, in this field, assessment items core to clinical reasoning considering sociocultural backgrounds are required.

Given the rapidly changing health care needs that affect services, systems, and staffing [8], digitalization is still recent, especially in PHN [19]. The COVID-19 pandemic has accelerated the shortage of PHNs and digitalization in Japan [20]. Approximately 70% of PHNs in Japan work as prefectural or municipal public servants [21] and work in various departments. As Japan has the world’s oldest population and the lowest birth rate, the national government must encourage digitalization and reduce the number of civil servants by half by 2040 [22]. Therefore, the total number of PHNs will potentially be halved by 2040. To ensure the quality of public health nursing, Japan has a national license system for PHNs [23]. Additionally, supervisory PHNs must manage practices in each department [24] while assessing the workloads of their staff and developing their competencies. Owing to the lack of ICT systems, supervisory PHNs may be unable to understand the happenings in each department and the performance and competencies of each staff member. An ICT system is needed to support their management and human resource development.

Furthermore, electronic record systems collect data on nursing care and promote evidence-based management in hospitals [6,10-13,25,26]. The Omaha system also enhances such management for each patient in community settings [14]. In Japan, the national government conducts a public health nursing activities survey every 3 years [27]. To this end, randomly selected prefectural or municipal PHNs gather data on their daily activities and the required hours [27]. However, no study has applied these data to elucidate public health nursing care management. To encourage evidence-based practices and nursing management, PHNs require an electronic recording and management system that identifies health needs and suggests the best public health nursing practices. The system would help PHNs think about their daily activities and share information with their supervisors to improve the quality of care and competencies, thus ensuring health equity in the community.

### Objective

This study will develop and validate an electronic recording and management system to evaluate the necessity of different public health nursing practices—including individual care, community-based activities, and project development—and to determine their best practices.

## Methods

### Study Design

This study used an exploratory sequential design, which was conducted in Japan [28]. This design was suitable for exploring unknown questions using qualitative methods and developing a new instrument that can be validated by quantitative research analysis [28]. This study has 2 phases. Phase 1 will include a panel discussion to develop a structure for the electronic recording and management system. Phase 2 will confirm the validity of the proposed items through interviews with expert PHNs and a nationwide survey of PHNs.

### Participants

The research team worked in public health nursing, home care nursing, public health, statistics, and computer sciences. This study is divided 2 phases. In phase 1, the research team conducted a literature review and a panel discussion that included 3 supervisors with experience working as prefectural or municipal government PHNs and 1 executive director of the Japan Nurse Association. The criteria for convening the expert panels meeting were to gather their opinions on the draft architectural framework—a hypothetical algorithm to determine the need for practice review; moreover, each item was developed by the research team.

In phase 2, the participants of interviews will be supervisory PHNs in prefectures or municipalities. Additionally, to ensure nationwide representation, we will include supervisory PHNs and midcareer PHNs with experience working in all local governments in Japan except those that completed the interviews. The inclusion criteria of midcareer PHNs have their cases and experience working for 6 to 20 years. The exclusion criteria for them are a managerial position.

### Recruitment

In phase 1, the research team recruited a panel of experts using snowball sampling. In phase 2, they recruited 5 to 10 supervisory PHNs as participants, who worked in prefectures or municipalities to avoid bias in the functions and roles of public health centers. Before starting the nationwide survey, we sent letters, including the study description, to supervisory PHNs. We used a mailing list of all supervisory PHNs from the Ministry of Health, Labour and Welfare to announce the survey by email. We expect approximately 530 local governments to participate based on a collection rate of 30% in a previous study that used a similar survey methodology [29].

### Procedures

#### Phase 1: Develop an Architectural Framework

Based on a literature review [6,25-27,30-32] and discussions at 10 meetings, the research team created an architectural framework (Figure 1) for an electronic recording and management system. This study reports the construction of the system in the blue background area, especially the development of the system input items, and the hypothetical algorithm based on the practical experiences in the red frame areas. The data will be stored on a server contracted by the research team. The system can be accessed via a web browser on a touchscreen device or personal computer. We will collect data through a web-based survey form and a cloud-based practice recording system. Statistical analysis will be performed based on the data, and the results will be presented on the dashboard view as tables or graphs. Figure 2 shows the hypothetical algorithm to determine the need for practice review. Based on each PHN’s assessment regarding individual care, community activities, and project implementation, an algorithm will suggest appropriate practices and directions for improvement.

**Figure 1 figure1:**
[figure not shown]
An architectural framework for an electric recording and management system.

**Figure 2 figure2:**
[figure not shown]
A hypothetical algorithm for determining the need for practice review.

#### Phase 2: Confirming the Validity of the Proposed Items

In phase 2, the validity of the proposed items will be tested using interviews with expert PHNs and a nationwide questionnaire survey of supervisory and midcareer PHNs.

The semistructured interviews with supervisory PHNs will be conducted over a web-based meeting system. We will confirm that the validity of the survey items comprising each unit constructed in phase 2 is relevant to the cases handled by PHNs (ie, to verify that the PHNs will be able to answer the question). We will send the survey items to the interviewees in advance, including the items comprising the unit constructed in phase 1 and a semistructured interview guide. To protect the interviewees’ privacy, we will not record the interviews. To ensure the trustworthiness of the qualitative phase and to protect the interviewees’ privacy, 2 researchers will conduct the semistructured interviews in pairs, one acting as an interviewer and the other taking notes. After the interviews, we will send a memo of the content to the interviewees over email for confirmation. Based on the results, we will revise each item in the system and finalize it.

The nationwide survey will be conducted using a web-based form, and a URL or QR code for the survey will be distributed to supervisory and midcareer PHNs. We will ask the research participants to (1) select one highly necessary and one less necessary element of individual care, community-based activities, and project development that they have performed within the last month; and (2) enter select cases into our system and summarize them. The level of necessity of each activity will be measured using a 10-point Likert scale from 1 (very unnecessary) to 10 (highly necessary). Additionally, we will ask participants about the importance and incomprehensibility of each item and whether to include any additional items. Responses will be sent directly to the researcher (ie, they will not go through the supervisory PHNs).

### Data Analysis

In the qualitative phase, 3 researchers will read the interview transcripts (confirmed by the interviewees) and classify the contents in terms of the survey items using the content analysis method [33]. We will combine expressions with similar meanings into a single concept, whereas contradictory data will be left as is. After consulting with the project’s supervisory PHNs, we will revise the survey items. The items for the nationwide survey will be finalized after all the project members confirm their validity.

The nationwide survey will be conducted through a descriptive analysis of the components of the system and the subjective necessity of PHN practices. In this survey, PHNs will answer based on 2 types of activities: (1) highly unnecessary and (2) highly essential. We want to compare these 2 categories and confirm whether the items will effectively work to help identify the differences between each activity in terms of necessity. We will use Cronbach α to measure the degree of agreement between the importance calculated when the responses were applied to the system developed in phase 1 and the subjective importance expressed by PHN interviewees. We will also perform a decision tree or random forest analysis with the PHN’s subjective sense of significance as the outcome and the system configuration items as explanatory variables. The model with the highest prediction accuracy will be compared with the system created in phase 1. Finally, the panels will verify the nationwide survey results to confirm the external validity and consider whether the system may be improved based on the findings.

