#### Daily Record System

The daily record system has 5 units: (1) demographic information of PHNs, (2) assessment of the necessity, (3) daily review, (4) activity selection, and (5) task load [34]. PHNs will enter related data daily, as described below.

Demographics of the PHN unit. PHNs will input their IDs, dates of their activities, districts, activity domains, and the time required for each activity.Assessment of the necessity unit. The “necessity unit” determines how necessary each PHN activity is. The necessity of an individual case is determined by checking an applicable option (applicable, not applicable, or unknown) for each of the necessity judgment items in the domain to which each case corresponds to determine clinical urgency and any problems. The level of necessity of community-based activities and project development practices will be determined by checking the transdomain items and recording the number of people—the activity and practice targets.Daily review unit. It evaluates PHN activities to determine whether they are appropriate and worth continuing. Items are distributed across the individual care, community-based activity, and project development subsets.Activity selection unit. It examines movements across the different types of PHN activities. Individual care practices include items that speak to or can develop into community-based activities and project development practices.Task load unit. It determines the difficulty level of each activity. Individual care difficulty will be measured using the Japanese version of the National Aeronautics and Space Administration task load index. This considers mental, physical, and temporal demands, level of effort, performance, and frustration [34].

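### Cronbach α is named to measure agreement between the system's calculated importance and the PHN's own rating, but for two scores it measures consistency and cannot support a claim of agreement

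*Protocol article*

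**What the plan says.** The Data Analysis section of the protocol article names the statistic and its purpose: "We will use Cronbach α to measure the degree of agreement between the importance calculated when the responses were applied to the system". The system meant is the one from phase 1. The other side of the comparison is given as "the subjective importance expressed by PHN interviewees". No threshold for α is given, and no other agreement statistic is named for this comparison.

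The subjective side is described under Phase 2: Confirming the Validity of the Proposed Items: "The level of necessity of each activity will be measured using a 10-point Likert scale from 1 (very unnecessary) to 10 (highly necessary"). Respondents are asked to "select one highly necessary and one less necessary element of individual care, community-based activities, and project development", so both high and low ratings are sought by design.

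The system side starts from a checklist. Under Daily Record System, the necessity of an individual case is judged by "checking an applicable option (applicable, not applicable, or unknown) for each of the necessity judgment items". Table 1 lists 44 transdomain necessity items for individual care, plus 2 to 20 domain-specific ones. The text does not say on what scale the resulting score is expressed. The algorithm is in Figure 2, which is not available here.

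The same section also plans a descriptive comparison of high- and low-necessity activities, a tree or forest model ("We will also perform a decision tree or random forest analysis with the PHN’s subjective sense of significance as the outcome"), a comparison of the best model with the phase 1 system, and verification by the panels.

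**The concern.** The question put to the data is whether the system gives an activity the same importance as the PHN does. That requires a measure that penalises systematic differences between the two scores. Cronbach α was built for a different question, namely how consistently several items measure one thing, and it contains no term for a difference in means.

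The algorithm is meant to show which practices need review. If it scored activities systematically lower than PHNs do, it could flag too few, and a high α would not reveal this. If its score runs on a different numeric range, α could instead look poor for a system that ranks activities well. Nothing else in the section measures system-PHN agreement. The high-versus-low comparison addresses discrimination, and the tree or forest model fits new rules that are judged on prediction accuracy.

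**Working it through.** The article gives no α value, threshold or sample size for this analysis, so there is no stated figure to reproduce. The check is of what α does with two scores.

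**Inputs.** From the article: two measures per case (Data Analysis) and a PHN rating from 1 to 10 (Phase 2). Assumed for illustration: the correlations r, the SDs, the SD ratios and the 3-point mean difference. Also assumed: the subjective importance in Data Analysis is the 1-10 necessity rating.

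**Formula.** For two scores X and Y,

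α = 2[1 − (Var X + Var Y)/Var(X+Y)] = 4 Cov/(Var X + Var Y + 2 Cov).

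The means do not appear, so adding any constant to X or Y leaves α unchanged.

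**Step 1: equal variances.** Here α = 2r/(1+r), which exceeds r whenever 0 < r < 1.
- r = 0.50: 1.00/1.50 = 0.67
- r = 0.54: 1.08/1.54 = 0.70 (shared variance 0.54² = 29%)
- r = 0.70: 1.40/1.70 = 0.82
- r = 0.80: 1.60/1.80 = 0.89

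**Step 2: a mean difference on a common scale.** The single-measure absolute-agreement ICC with equal SDs s and mean difference d is, in large samples,

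ICC = r s²/(s² + d²/2).

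Take r = 0.70 and d = 3, so d²/2 = 4.5. α is 0.82 throughout.

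| Assumed SD | ICC | α |
|---|---|---|
| 2 | 2.8/(4 + 4.5) = 0.33 | 0.82 |
| 3 | 6.3/(9 + 4.5) = 0.47 | 0.82 |
| 3.5 | 8.575/(12.25 + 4.5) = 0.51 | 0.82 |

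With d = 0 the ICC equals r, here 0.70. So part of the gap arises even without an offset, because α for two measures is the average-measure consistency ICC.

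**Step 3: different scales.** Let the system SD be c times the PHN's SD. Then α = 4rc/(1 + c² + 2rc). With r = 0.80:
- c = 1: 3.2/3.6 = 0.89
- c = 2: 6.4/8.2 = 0.78
- c = 3: 9.6/14.8 = 0.65
- c = 5: 16/34 = 0.47

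The correlation and the ranking are the same in all four rows; only the units change. Even a perfectly proportional score (r = 1) with c = 4.4 gives 17.6/29.16 = 0.60.

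Steps 2 and 3 are alternatives. Step 2 needs a score on the PHN's scale, and step 3 needs one that is not.

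**The case against.** The strongest reply is that little hangs on α. The article does not rank its analyses, attaches no cut-off to α, and also plans interviews, a high-versus-low comparison, a predictive model and panel review. This stands. A reader might infer that α is the central validity criterion and that the study's main conclusion would fail with it. The document does not say so, and the 0.70 used above is only a reference point.

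A second reply concerns the illustrations. It is tempting to cite a system that always scores exactly 4 points below the PHN, giving α = 1.00 with a low ICC. That would require every PHN rating to be 5 or higher on a shared 1-10 scale. This fits poorly with a design that asks for a less necessary activity of each type. The same design probably widens the SD, which raises the ICC. For these reasons the working uses a mean difference with imperfect correlation and shows a range of SDs. The contrast shrinks as the SD grows but does not vanish.

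Third, the scale of the system score may be given in Figure 2. If the score is an arbitrary item total, an absolute offset has no meaning and consistency is the relevant property. That too is fair: α would then be mislabelled rather than empty, though it would still depend on units. A reader might conclude that the analysis fails in both directions at once. The text supports only one or the other, depending on a figure not seen.

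Fourth, the article does not say outright that the comparator is the 1-10 rating; the Phase 2 section also asks about the importance of each item. The pairing is plausible but inferred. It affects the numbers, not the fact that α is assigned to agreement.

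**Conclusion.** The point holds as a should-fix. The article assigns a consistency coefficient to a question of agreement, and it does so explicitly, so this is not a detail left to a fuller plan. A high α cannot be reported as agreement between system and PHN. With r = 0.70 and an assumed 3-point mean difference, α is 0.82 against an absolute-agreement ICC of 0.33 to 0.51 for SDs from 2 to 3.5. If the scales differ, α at r = 0.80 can fall from 0.89 to 0.65 or 0.47 with no change in ranking. The SDs, the offset and the correlations are assumptions; the insensitivity of α to a mean difference is algebraic.

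Two limits apply. A very low α on a common scale would still signal a weak relation, so the fault lies in reading a high value as agreement. And changing the statistic does not cure the effect of choosing extreme cases. In simulated data with clearly separated high and low cases and no relation within either group, α was 0.977 and the ICC was also 0.955.

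**What to change.** Replace α for this comparison, and state which PHN rating is the comparator.

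- **If the phase 1 algorithm yields a 1-10 score**, or one converted to 1-10 by a rule fixed before the survey data are seen and not fitted to the PHN ratings: report the single-measure absolute-agreement ICC or quadratic-weighted kappa, plus the mean difference with limits of agreement. A conversion fitted to the ratings would remove the very offset that the ICC should detect.
- **Otherwise:** report Spearman's or Kendall's rank correlation and call it association, not agreement.
- **In both cases:** use confidence intervals clustered by PHN, because each respondent supplies several activities.
- **Keep α** only for internal consistency of multi-item units.

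The cost is a short change to the Data Analysis section and a few lines of code, with no new data. The reported figure will probably look less favourable than α would. The abstract reports data collection as complete, so a conversion rule written now must be shown not to have drawn on the ratings. If that cannot be shown, the rank correlation is the safer choice.

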**Termly review system (N=57)**							
	Necessity: data available that support the necessity						12

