	**Termly review**						
		Prediction and evaluation: initial health issue resolved and low probability of relapse				10	
		Disparity: inequity in service provision between regions or target groups				3	
		Substitutability: alternative private services available				5	
		Institutional issue: end of the year as a subsidized project				2	
		Resource: lack of cooperation with key persons in the district				8	
		Aggregated: long-term and large number of PHN inputs determined the project is less necessary				3	

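### At least one community/project item used as a predictor can be read as the necessity judgement it is meant to predict, so accuracy and item importance there may be partly circular

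*Protocol article*

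**What the plan says.** The Data Analysis section sets up the model with the PHN's subjective rating of significance as the outcome and "the system configuration items as explanatory variables". It restricts the predictors to no unit or type of item. The most accurate model is then compared with the system built in phase 1.

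The section on phase 2 describes how the data arise. Respondents are asked to "select one highly necessary and one less necessary element of individual care, community-based activities, and project development", and then to "enter select cases into our system and summarize them". On the rating it says: "The level of necessity of each activity will be measured using a 10-point Likert scale from 1 (very unnecessary) to 10 (highly necessary".

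Table 2 prints example items for community-based activities and project development. Three places bear on this point:
- The Aggregated category of the termly review (3 items) has the example "Aggregated: long-term and large number of PHN inputs determined the project is less necessary".
- The Necessity category of the termly review system (12 items) is printed as "Necessity: data available that support the necessity".
- The daily review unit (3 items in Table 2, 9 in Table 1) is described in the Daily Record System section: "It evaluates PHN activities to determine whether they are appropriate and worth continuing".

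**The concern.** The study wants to make PHNs' tacit judgement explicit and to confirm that the items separate more from less necessary activities. That needs predictors that describe the case, activity or project. If a predictor already carries the respondent's verdict, a tree can reach good accuracy by splitting on it, and a forest can rank it above the descriptive items. Both results would then partly show that a PHN's answers agree with each other.

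An internal train/test split gives no protection, because the overlap is present in every record, held out or not. Accuracy also selects the model that is compared with the phase 1 system, so the problem would carry into that comparison.

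**Working it through.** The documents give no accuracy figure to reproduce, so the check is mainly textual, with the item counts re-added.

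**Counts.**
- Table 1, transdomain: 5 + 44 + 9 + 6 + 5 = 69. Adding 2 to 20 domain-specific items gives 71 to 89 daily items, as printed. Termly: 4 + 10 = 14, as printed.
- Table 2, daily: 5 + 4 + 3 + 2 + 12 = 26, as printed. Termly: 12 + 10 + 3 + 5 + 2 + 8 + 3 + 10 + 4 = 57, as printed. Together 26 + 57 = 83.

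**Which printed items overlap with the outcome?**
- Aggregated (3 items): the example contains the conclusion that the project is less necessary. Whether it means a conclusion reached from heavy PHN input, or heavy input to a project already judged less necessary, it is hard to tick without that verdict.
- Termly Necessity (12 items): the example asks whether supporting data exist. This is partly a checkable fact, so the overlap is weaker.
- Daily review (3 items in Table 2): the unit's stated purpose is a judgement about continuing, but its printed example, lower attendance than expected, is observable. The Table 1 example, a worsening problem, describes the case.
- Individual care (Table 1): the printed necessity items are mostly case facts such as acute deterioration, dependence in daily living or domestic violence. None states how necessary the care is.

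The category with explicit verdict wording therefore holds 3 of 83 items (3/83 = 3.6%). All three places together hold 3 + 12 + 3 = 18 of 83 (21.7%). Neither figure counts judgement items, because only examples are printed.

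**Does held-out testing expose it?** A small simulation shows the direction only. All its inputs are assumptions: 350 records, half high and half low necessity; 20 descriptive items; a linear classifier scored on a held-out half; and one added verdict item that agrees with the outcome with probability q.

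| Descriptive items | Without verdict item | q = 0.7 | q = 0.8 | q = 0.9 |
|---|---|---|---|---|
| Uninformative | 0.50 | 0.66 | 0.79 | 0.90 |
| 8 of 20 informative (prevalence 0.3 vs 0.5) | about 0.68 | 0.73 | 0.80 | 0.90 |

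At q = 0.5 there is no gain. Held-out accuracy rises with q, so a split sample does not reveal the overlap. Because q is assumed, the table says nothing about the size in this study.

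**The case against.** The strongest reply is that the evidence rests on one ambiguous example. It sits under an aggregated heading, and the Termly Review System section says that some termly items are checked automatically from accumulated reports, so it may summarise past entries instead of the respondent's present opinion. This stands as a limit on certainty. It does not remove the overlap if those entries come from the same PHN, and the documents do not say that this category is filled automatically.

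A second reply is that PHN judgement belongs in the system: the phase 1 section says the algorithm works from each PHN's assessment. This also stands. Taking judgement items out of the system score would test a different system, so it is not asked for here.

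A third reply is that the tables show phase 1 output, that items are finalised after the interviews, and that a condensed article may leave item-level selection to a fuller plan. In part this is fair. Yet the article does state the predictor set, and without exclusion.

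A reader might go further and infer that the outcome is literally among its own predictors, that a tree must split on a verdict item first, or that the whole model is affected. The documents do not support this. The 1-10 rating is not a listed predictor, the order of splits depends on data not shown, and the visible wording concerns community/project items only. Nor do they say that rating and items are completed in one session, or in which order, so no fault in screen order can be claimed.

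**Conclusion.** The point holds in a limited form. No predictor is excluded, at least one printed community/project item can be read as expressing the necessity judgement, and the same PHN supplies outcome and predictors for an activity chosen by its necessity. Accuracy and item importance for community-based activities and project development may therefore be partly circular.

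The size is unknown. The category concerned holds 3 of the 83 items in Table 2, and one item could be enough to matter if it tracks the rating closely. No corresponding item is visible among the individual-care examples.

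Two assumptions carry the conclusion. First, the subjective significance named in Data Analysis is taken to be the 1-10 necessity rating, the only subjective activity-level rating described. Second, the printed item, or one like it, is taken to remain in the final list and to be answered in the survey.

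**What to change.** Before analysis, label every item on the final list as a descriptive feature or as a judgement of necessity or continuation. Do this item by item, since a unit such as daily review may hold both kinds. Fit the tree or forest, and compute the comparison with the phase 1 system, both with and without the judgement items, and do so separately for individual care and for community/project activities. Base any statement about which items explain necessity on the version without them. The difference between the two versions shows how much the judgement items contribute.

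The cost is one labelling pass, a sentence or two in Data Analysis, a little more analysis and probably a lower reported accuracy. No new data are needed. This matters because the Abstract reports data collection as completed in January 2023, although the Results overview still describes the survey as upcoming.
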